### Health-economic evaluation

Missing cost and effect data will be imputed, using MICE. Two multilevel models will be specified, one for costs and one for effects, which consider the hierarchical structure of the data [105]. For effects, normal-based 95% CIs will be estimated. For the costs, 95% CIs will be estimated using bias-corrected and accelerated bootstrapping with 2,000 replications [106]. For this, cluster bootstrapping will be used, which is recommended for resampling hierarchical data [107]. The incremental cost-effectiveness ratio will be estimated by calculating the difference in costs between treatment groups divided by the difference in effectiveness of the treatment groups. The joint uncertainty surrounding costs and effects will be summarised using cost-effectiveness planes and cost-effectiveness acceptability curves [108]. To test the robustness of the base-case findings, probabilistic sensitivity analyses will be done by changing several assumptions made in the base-case scenario (e.g. about unit costs and volumes). The health-economic evaluation will be conducted using Stata.

### Qualitative effect evaluation

In order to answer **RQ III**, a qualitative effect evaluation will be performed. Its aim is to describe which interventions the participants used and how they benefited from them, how the interventions influenced their experience and actions in the RTW process, and which typical trajectories can be reconstructed in this context. For this purpose, both the participant´s implicit and explicit knowledge will be recorded.

For the qualitative sub-sample, study participants potentially interested in being interviewed (*n* = 30) from different study centres will be selected according to the following characteristics from the above recruited study population:IG and CG: 20 interview participants from the IG; and 10 participants from the CG (2:1 ratio),Gender-specific differences and similarities: men and women will be interviewed in a 1:1 ratio per group,Main ICD-10 diagnosis: proportionally, the most frequent MDs out of the total study population will be selected,Different subjective RTW expectations, andOther: variety in educational qualifications, company sector and size will be considered. In the sense of theoretical sampling [109], it will be decided after the analysis of the first interviews, which further characteristics might be of interest for the RQs.

### *Data collection and analysis*

The study participants will be interviewed at two time points. The pre-interviews take place at the beginning, after completion of the baseline survey and allocation (T0), either via face-to-face on site at the study centres, or by telephone or video call. The post-interviews will be conducted after the intervention (T3, 18 months) by telephone or video call (see Fig. 1). The duration of each interview will average 60 to a maximum of 90 min. All study participants will receive compensations for their study related efforts (€20 for each qualitative interview conducted). All interviews will be digitally recorded and transcribed in a pseudonymised form. The semi-structured interviews will include a narrative-generating main part as well as a reflexive and theoretically guided evaluative part.

The following topics will be considered for the pre-interview: (a) conditions under which the current crisis of MDs arose, (b) coping strategies used to deal with the disorder, (c) possible fears, hopes, and other factors that promote and inhibit a SRTW, (d) work-relatedness of the treatment, and (e) expectations with regard to the intervention. In contrast, the following post-interview topics will be covered: (f) experience and actions during and after the (gradual) reintegration, (g) self-confidence, trust, social support by the company and workplace accommodation changes during the RTW process, (h) promoting and inhibiting factors during the return to work, (i) support offered by the RTW experts as well as the experiences with the interventions, and their evaluations.

The Documentary Method of Interpretation for interview analysis [110, 111] will be used to elicit explicit knowledge (e.g. conscious, communicable skills and competencies, opinions, evaluations, and assessments) and tacit knowledge (e.g. internalised skills, orientations and knowledge based on experience). The six analysis steps will be as follows: creation of a thematic course per interview, identification of the narratively dense passages, formulating interpretation, reflective interpretation, case description per person and case comparisons and type formation. All interpretations and analyses will be discussed regularly by the qualitative research team to reach consensus.

## Process evaluation

In order to answer **RQ IV**, a multimethod process evaluation will be performed. The purpose of the extensive process evaluation is to assess the contextual factors, the implementation process, the framework conditions of RTW-PIA as well as the experiences of the study participants from the IG and the IG-treatment providers. The process evaluation will be guided by the proposed indicators from the theoretical framework of Linnan and Steckler [112] which have been aligned with RTW-PIA´s study context and its three core modules (A-C) (Table 3).

**Table 3 Tab3:** Process indicators, data collection method

**Process indicators**	**Level**	**Operationalisation**	**Data collection method**
***Fidelity*** Adherence to the intervention manual and intervention delivery of Module B	IG-TP	Statements (ratings, yes/no) Reasons Suggestions for manual improvement	Evaluation sheets (Module B) Focus groups
***Dose delivered*** The extent to which each Module´s component (A-C) of RTW-PIA was actually delivered according to the intervention plan	IG-TP, IG	Number, date, and duration of every module´s sessions	Participant-related documentation sheet Technical log file (Module C)
***Dose received***	IG	Dose-response	Participant-related documentation sheet Needs-oriented evaluation sheet (Module A)
***Reach*** Actual proportion of participation in each Module (A-C) of the RTW-PIA intervention	IG	Characteristics of SC Characteristics of study participants Drop-out and reasons	Participant-related documentation sheet
***Satisfaction I*** Study participant´s satisfaction with RTW-PIA Modules (A-C) and the overall intervention	IG, Qualitative sub-sample	Satisfaction rate Quality rate Experiences	Online surveys (T1-T3) Post-Interview Technical log file (Module C)
***Satisfaction II*** Treatment provider´s satisfaction with RTW-PIA implementation	IG-TP	Experiences	Focus groups
***Context I*** Contextual factors and history that have an impact on the effectiveness of the intervention	Qualitative sub-sample	Description of barriers Description of facilitators	Pre-Interview Post-Interview
***Context II*** Contextual factors and history that have an impact on the effectiveness of the intervention	IG-TP	Description of barriers Description of facilitators	Focus groups
***Recruitment*** Procedures used to approach and attract patients; number of invited patients; reasons for non-participation	SC	Description of approaches	Logbook Weekly recruitment sheet Focus groups Anonymous non-response questionnaires

Abbreviations: *IG* Intervention group, *IG-TP* Intervention group-treatment providers, *SC* Study centre. For further information regarding time of measurements (T1-T3), please see Flow Chart (Fig. 1) or study schedule of interventions and assessments (Table 2)

The study population of the quantitative process evaluation will equal the participants of the IG (*n* = 253) from the above recruited study population and the participants of the CG from the qualitative sub-sample (*n* = 10). A sub-sample of IG-treatment providers from different study centres will be included as well.

### *Data collection and analysis*

Quantitative data collection of the process evaluation will take place for each IG-study participant in a pseudonymised form throughout the 18-month RTW-PIA treatment period. An overview of the key process indicators and the multimethod data collection approach is provided in Table 3. The quantitative data will be analysed by means of descriptive statistics (e.g. frequencies, means, summed up ratings). The pre- and post-interviews in the qualitative evaluation will complement the results of the process evaluation. Influential contextual factors will be recorded, evaluated, and processed. Specific information regarding their experiences and satisfaction with RTW-PIA will be collected from the IG-participants in the post-interview (*Satisfaction I*, Table 3). Furthermore, three qualitative focus groups will be conducted during the intervention period with a sub-group of involved IG-treatment providers from each study centre (*Fidelity, Satisfaction II,* and *Context I*, Table 3). All focus group meetings will be digitally recorded, transcribed in a pseudonymised form, and subsequently analysed thematically via qualitative content analysis, e.g. Kuckartz [113].

### Ethical aspects

The study protocol has been ethically approved by the principal Ethics Committee at Hanover Medical School. All original documents will be treated confidentially in line with German Federal Data Protection Act. A comprehensive data protection concept has been approved by the data protection officer of the Hanover Medical School. The contact details of participants will be stored separately in the respective study centre in locked cabinets or on secured servers and are only accessible to authorised staff. The evaluation data will be pseudonymised and stored on secured servers within the evaluator´s settings and be accessed only by authorised persons. A unique study identifier will enable the study participant´s online survey-, qualitative- and administrative data to be linked.

Even if rare, negative effects of psychotherapy cannot be completely ruled out [114]. The multidisciplinary treatment teams from each study centre will inform the evaluators about any occurrence of spontaneously reported adverse events and other unintended effects of the trial; the evaluators will document this information. With regard to the completion of the online survey, only few complications are expected since it contains mostly validated and frequently used instruments. At the end of each online survey assessment, participants will be reminded and advised to contact their respective psychotherapeutic treatment provider if the state of their health deteriorates. No interim analyses of data will be required or planned within the study due to its primary endpoint. A data monitoring committee has not been set up in the present study.

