#### CAU

CAU is customised according to the participant´s disorder, degree of severity, and associated impairments. Since the exposure to CAU can vary depending on the participant´s needs, the total duration of CAU was defined to last at least six months. The number of contacts in three months usually varies between 3 and 5, which can be 1 to 3 medical appointments, and 2 to 4 other appointments, e.g. social work consultations and appointments with a psychologist to coordinate non-medical treatment options (e.g. sports activities, ergotherapy, psychological counselling, and group therapy). Unlike RTW-PIA, CAU does not focus specifically on work, work ability, and RTW.

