#### RTW-PIA in conjunction with CAU

RTW-PIA is an 18-month, multimodal, clinical and work-directed intervention that focuses on the individual, i.e. employees with MDs. RTW-PIA consists of three core modules (A-C) that systematically build on each other. Table 1 describes the RTW-PIA core modules in line with the Template for Intervention Description and Replication (TIDieR) checklist [70]. The modules will be organised and implemented by trained multidisciplinary psychotherapeutic treatment teams employed by the respective POCs. The exposure to each module may vary depending on the participant´s needs. IG-participants can receive up to 20 sessions in total (Module A: 3–8 individual sessions, Module B: 6–9 group meeting sessions, Module C: 1–3 video call sessions) besides CAU.

**Table 1 Tab1:** Brief description of the RTW-PIA core modules according to the TIDieR checklist

*Brief name*	**Module A**. Individual RTW support	**Module B**. RTW aftercare group meetings	**Module C**. Web-based aftercare
*Why*	The aim is to provide professional support to the participants by assessing their current professional and personal obstacles and resources when returning to work. Helpful and hindering factors of the working environment will be assessed.	The aim is to develop confidence in the RTW process by strengthening the participant´s work ability and self-efficacy through mutual support, group cohesion and stigma reduction.	The aim is to facilitate a behaviour change during as well as after the RTW course so as to implement it in everyday work life. Participants should prepare themselves to deal proactively with inevitable crises and challenging working conditions so as to prevent future relapses.

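### Adverse events are recorded only through spontaneous reports to treatment teams, whom intervention participants meet more often, so event counts by arm are not comparable

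*Protocol article*

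**What the plan says.** **Harm capture.** Under Ethical aspects, the treatment teams at each centre "will inform the evaluators about any occurrence of spontaneously reported adverse events and other unintended effects of the trial", and "the evaluators will document this information". At the end of each online survey, "participants will be reminded and advised to contact their respective psychotherapeutic treatment provider if the state of their health deteriorates". The article describes no other adverse event route.

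**Contact in both arms.** Under CAU, "The number of contacts in three months usually varies between 3 and 5", and "the total duration of CAU was defined to last at least six months". No maximum duration is given.

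**Additional contact in the IG.** "RTW-PIA is an 18-month, multimodal, clinical and work-directed intervention", and "IG-participants can receive up to 20 sessions in total": 3 to 8 individual sessions (Module A), 6 to 9 group meetings (Module B) and 1 to 3 video calls (Module C). Table 1 places Module A in the first six months, Module B in the first twelve, and Module C from month 6 for twelve months, with written feedback from the provider. The Interventions section says that a separate team, one that does not carry out CAU, delivers these modules.

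**Blinding.** Under Allocation and blinding, neither participants nor treatment providers are blinded.

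**The concern.** A spontaneous report needs an occasion on which to make it. Here the occasion is contact with a clinic team, and the amount of that contact is set by randomisation. The IG keeps everything the CG has and adds sessions, a second team and a longer programme. With identical true harm in the two arms, more of it would be expected to reach the record in the IG.

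The surveys go to both arms on one schedule and could remove this imbalance. The article uses them instead to direct a deteriorating participant back to the provider, which is the unequal channel.

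What is at stake is the interpretation of harms. The protocol accepts that negative effects of psychotherapy are possible and foresees adoption into standard care if results are promising. An excess of recorded events in the IG could reflect contact alone. A genuine harm, for example from an unsuccessful return to work, could be explained away as contact-driven. The documented events cannot separate the two.

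**Working it through.** The article states no figure for harms, so the check is a count of provider contacts by arm.

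**Inputs**
- CAU rate, both arms: 3 to 5 contacts per three months (section CAU).
- CAU duration, both arms: at least 6 months (section CAU). Durations of 12 and 18 months are assumptions, used to show the range.
- IG extra sessions: minimum 3 + 6 + 1 = 10; maximum 8 + 9 + 3 = 20. The maximum matches the protocol's own total.

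**Formula.** CG contacts C = rate × (months of CAU / 3). IG contacts = C + extra sessions E. Ratio = (C + E) / C, with the same CAU use in both arms.

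**First six months.** Module A falls wholly in this window (3 to 8). Module B, spread evenly over twelve months, contributes half (3 to 4.5). Module C has not begun. So E = 6 to 12.5 and C = 6 to 10.
- Lowest ratio: (10 + 6) / 10 = 1.6
- Highest ratio: (6 + 12.5) / 6 = 3.1

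**Whole 18-month programme.** E = 10 to 20.

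| CAU lasts | CG contacts | IG contacts | Lowest ratio | Highest ratio |
|---|---|---|---|---|
| 6 months | 6–10 | 16–30 | (10+10)/10 = 2.0 | (6+20)/6 = 4.3 |
| 12 months | 12–20 | 22–40 | (20+10)/20 = 1.5 | (12+20)/12 = 2.7 |
| 18 months | 18–30 | 28–50 | (30+10)/30 = 1.3 | (18+20)/18 = 2.1 |

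The ratio exceeds 1 in every row, because E is added to the same C.

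**What this could do to counts (illustration only).** Assume equal true harm, CAU at 4 contacts per three months, and a participant with an event who mentions it with probability q at each contact, independently. The proportion recorded is 1 − (1 − q)^contacts. For q = 0.05 and six months of CAU (C = 8):
- CG: 1 − 0.95^8 = 0.34
- IG with E = 10: 1 − 0.95^18 = 0.60, ratio 1.8
- IG with E = 20: 1 − 0.95^28 = 0.76, ratio 2.3

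| q | CAU 6 months (C = 8) | CAU 18 months (C = 24) |
|---|---|---|
| 0.05 | 1.8–2.3 | 1.2–1.3 |
| 0.10 | 1.5–1.7 | 1.1 |
| 0.20 | 1.2 | 1.0 |

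The documents give no value for q, so this shows how the mechanism behaves and does not estimate the bias. It also treats a group session as equal to an individual one.

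**The case against.** **No between-arm harm test is announced.** True: the article says only that reports are documented. But any account of those events by arm carries the contact imbalance, and nothing in the article warns against reading them that way. The Discussion acknowledges performance and expectancy bias, not this.

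**Symmetric deterioration data already exist.** The BSI-18 is a secondary outcome at five time points in both arms, and the PHQ-9 and TiC-P are also collected. This stands in part, and it makes the fix cheap. However, the planned analysis tests a difference in mean latent slopes, which does not count individuals who deteriorate, and Ethical aspects gives the BSI-18 no role in assessing harm.

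**The questionnaire may already ask about unwanted effects.** Table 2 and Additional file 1 are not shown, so its absence cannot be asserted. The proposed item is conditional for that reason.

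**Contacts are not equal reporting opportunities.** Up to nine of the 20 sessions are group meetings of 3 to 9 people. This stands and weakens the ratios as a measure of reporting, though not their direction.

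**Stronger readings that the documents do not support.**
- A reader might infer that a CG participant who deteriorates once CAU has ended cannot enter the record. Each survey, in both arms, advises contacting the provider, and CAU has no stated maximum. The route is weaker, not absent.
- A reader might apply 2.0 to 4.3 to the first six months. That range sets IG sessions spread over up to 18 months against six months of CG contact; within six months it is about 1.6 to 3.1.
- A reader might treat the statement that "A data monitoring committee has not been set up in the present study" as making this worse. A committee would not correct unequal spontaneous reporting, so its absence adds nothing here.

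**Conclusion.** The point holds as a flaw in a method that the protocol states. Ascertainment of adverse events depends on arm, and by-arm counts of the documented events should not be interpreted as a comparison of harm. Recording is likely to be more complete in the IG. That direction follows from adding sessions and a second team to the same CAU. It assumes that CAU use is similar in the two arms and that the CAU and RTW-PIA teams both report; the article does not say which teams do.

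The size of the bias cannot be computed. The contact ratio is about 1.6 to 3.1 in the first six months (Module B spread evenly). Over 18 months it runs from 2.0 to 4.3 if CAU ends at its minimum, down to 1.3 to 2.1 if CAU continues throughout. The sample size and the primary and secondary effectiveness analyses are unaffected. The change is worth making because it is inexpensive and the harm record cannot otherwise be compared between arms.

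**What to change.** 1. Report spontaneous events descriptively, by arm and by source (CAU team, RTW-PIA team, other), and state that counts are not to be interpreted between arms.
2. Base the between-arm harm comparison on data collected identically in both arms: the proportion of participants with clinically relevant worsening on the BSI-18, with the threshold fixed before database closure. Add the PHQ-9 if the assessment schedule, not shown here, has it at follow-up.
3. Use psychiatric admissions from the TiC-P as supportive only. Its recall is three months and the surveys are six months apart. If it is asked at all four follow-ups, it covers 4 × 3 = 12 of 24 months.
4. If the questionnaire does not already contain one, add one identically worded question on unwanted effects to the remaining T1 to T4 surveys in both arms.

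**Cost.** One short table from data already planned and, if needed, one survey item through a minor amendment. The survey becomes slightly longer. Recruitment began in September 2021, so surveys completed before the change will lack the item, and its results should be reported with that denominator. Answers to the new item remain unblinded self-report, but they are requested on the same schedule in both arms.

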## Discussion

This study protocol describes the design of a study to evaluate the (cost-)effectiveness and implementation process of a multimodal, clinical and work-directed intervention, called RTW-PIA. By combining face-to-face individual RTW support, RTW aftercare group meetings as well as a web-based aftercare, RTW-PIA aims to support sick-listed employees with MDs to achieve SRTW. Although a recent review has demonstrated that RTW interventions combining both workplace components and clinical interventions could possibly help depressed employees to RTW faster and reduce the duration of sickness absence [27], it remains unclear which type and combination of clinical and work-directed interventions are effective and what the underlying mechanisms for their effectivity are.

We hypothesise that employees who receive RTW-PIA in conjunction with CAU will more frequently achieve SRTW at 12 months after first having returned to work, compared to those exposed to CAU only. In terms of cost–benefit ratio, we expect that RTW-PIA in conjunction with CAU will be superior to CAU only, thus generating cost savings for social insurance funds, companies and society as a whole. With respect to the qualitative evaluation, we strive to provide an in-depth analysis of how and under what conditions employees (do not) benefit from RTW-PIA. Within the framework of the multimethod process evaluation, we anticipate that our predefined key indicators will have an impact on the implementation of RTW-PIA.

The present study has some important strengths. Applying a randomised controlled study design will be the most appropriate method when evaluating the (cost-)effectiveness of RTW-PIA on the employees´ achievement of SRTW. We will include patients with a wide range of MDs to reflect the contemporary clinical practice in Germany. The present study will make an important contribution to the international research field of RTW by implementing an observation period of two years, enabling to examine long-term effects such as the sustainability of the employees´ RTW. By collecting and combining a considerable amount of outcome data on the (cost-)effectiveness and implementation process from several stakeholder perspectives, this multimethodological evaluation design will capture various facets of RTW-PIA in practice and will add to the evidence base for the optimisation of SRTW practices. In addition to publishing our results in international research journals, a revised RTW-PIA manual will be provided for practical use as well as the amended web-based aftercare, which is closely linked to the manual content-wise. Finally, the generalisability of our results across Germany will be supported by the participation of different POCs with both urban and rural contexts, distributed over four German federal states.

Despite this extensive evaluation design, this study faces some methodological limitations. Since there is no central register-based data available on the employees’ SA in Germany, we have to deal with self-assessed data. To minimise possible recall bias, participants will be asked to record the days of SA consecutively in a list provided by the study centres. In addition, the study participants and treatment providers cannot be blinded to the group allocation due to the psychosocial nature of the RTW-PIA modules. Therefore, the risks of both performance bias and subject expectancy bias are difficult to prevent and will be considered when interpreting the final results. Due to the COVID-19 crisis and its aftermath, we expect some challenges with regard to the recruitment of study participants and implementation of RTW-PIA within the clinical setting of POCs due to lower occupancy rates of the clinics, staffing shortages and hygiene measures. However, any possible deviations from the protocol with regard to the recruitment or delivery of RTW-PIA will be continuously documented and considered in the final evaluation.

To conclude, this protocol outlines the comprehensive, multimethodological evaluation design of a multimodal, clinical and work-directed RTW-intervention. To the best of our knowledge, this evaluation study to examine SRTW among employees with MDs is the first of its kind. In case of promising results, RTW-PIA may be integrated into standard care within various German POCs. This, in turn, could be of significant public health and economic relevance, considering the high prevalence of MDs, their large burden of disease and economic impact on social security systems and labour markets [7].

This study goes beyond the process of return to work by emphasising sustainable RTW with a two-year observation period. It focuses not only on health-related but also on work-related outcomes such as participant’s work ability, RTW self-efficacy, and job satisfaction. Due to its long-term perspective and comprehensive evaluation design, this study can advance knowledge in the international research field of RTW. Our findings can moreover be essential for health policy makers and other experts in the field to further develop evaluation studies and interventions targeting SRTW practices at the intersection of the mental health care system and the workplace.

